Upon signing the consent form and enrolling in this research study, all women will be scheduled for their first of 3 study visits approximately 6 weeks postpartum. The consent form will include language to allow study staff access to the medical record information to confirm medical diagnoses by the inclusion criteria stated above. Subjects who do not have medical conditions as defined by the inclusion criteria stated above documented in their medical records will not be eligible to continue in the study. If a subject becomes pregnant during the course of the study, she will be asked to be followed during the pregnancy to determine occurrence of pregnancy complications and gestational weight gain.

Study Visits

At study visits, all women will be assessed for clinical outcomes, behavioral outcomes, mediating variables, and moderating variables (see table 3). Clinically relevant labs (pregnancy tests, OGTT, fasting glucose, HbA1c, TSH, LDL, triglycerides) will be reviewed when results are available. All subjects will complete approximately 45 minutes of questionnaires at study visits.

In accordance with ADA recommendations and UCH standard of care guidelines for postpartum diabetes screening for patients with prior GDM, which suggest 6 week postpartum glycemic status check via oral glucose tolerance test (OGTT), all enrolled subjects with a history of GDM will be offered an OGTT. Study staff will schedule this visit and with the subject’s permission, share OGTT results with subject’s pregnancy care provider (MD or CNM), thereby eliminating the scheduling of duplicate lab appointments. We anticipate this collaboration with OB caregivers will be welcomed, as published data demonstrate clinicians have a difficult time getting these women in for their 6 week postpartum OGTT – less than 50% of women had a 6 week postpartum OGTT.^[[42]](#endnote-42)^

All subjects will be instructed to arrive fasting to study visits, i.e. nothing except water for 10 hours prior to study visit. At study visits up to 50 cc of blood will be drawn, including fasting bloods and optional blood for storage.

During the first study visit, all enrolled subjects will be randomized using previously described permuted block scheme to either control or intervention arm.

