2) Lifestyle CoachA registered dietitian (RD) with training in patient-centered counseling techniques will work with the participants to help them set and achieve goals. The lifestyle coach will provide feedback, advice, and support through the *Fit After Baby* app, and via text messages and email messages. She will prepare to answer questions related to content for each week, how to use the app, and be available to answer any other questions the participant may want answered.

A study physician trained in patient centered counseling will periodically review email and text interactions, as well as notes from phone calls, to ensure adherence to these techniques. The coach and study physician will view progress of participants through a dedicated portal via an android coaching app where they can track diet, physical activity, weight, and progress towards individualized goals.

After a subject has completed the 12 month visit, we will send results of fasting glucose, lipid profile, hsCRP, HbA1c, and TSH from all study visits. The results will be accompanied by a letter from the study physician.

For women who completed their 6-week visit but do not complete their 6 or 12 month visits, we will attempt to reach them by phone, text, email, and/or mail. Additionally, during the consent process, we will get permission from subjects to contact a family member or friend if we are having trouble getting in touch with the subject at any point in the study.

Study Outcomes:

The primary outcomes are change in weight from baseline to 6 months and to 1 year postpartum (exit study visit), and change in weight from self-reported pre-pregnancy weight to one year postpartum.

Secondary outcomes**:** We will assess engagement and satisfaction with the program as potential mediators, defined as use of the app, adherence to self-monitoring of weight, diet, and physical activity, and interactions with the lifestyle coach. To assess changes in cardiometabolic risk factors we will obtain: blood pressure, waist circumference, and biomarkers at baseline, 6 months, and 12 months. We recognize that some of these measurements will be elevated in the postpartum state, however we hypothesize that we will see a greater change among women randomized to the intervention program. We will also assess sleep adequacy and appetite using scales embedded in the app and also sleep data from the Fitbit.

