**6 months**

6 month visit

**Measures:** Body weight and height: We will determine weight, measured twice wearing light clothing. We will obtain pre-pregnancy weight by self-report. Others have shown a high correlation (R=0.99) between self-reported and clinically measured pre-pregnancy weight.^[[45]](#endnote-45)^ We will measure height and use kg/m^2^ to determine BMI. 2) Demographics: We will collect age, self-reported ethnicity and race, working status, parity, family history of diabetes and cardiovascular disease, prior personal history of pregnancy complications, education level, marital status, number/ages of children living at home, and number of other household members. 3) Pregnancy test: We will obtain urine for rapid determination of hCG at the follow-up visit at 6 and 12 months postpartum. If the test is positive the participant will be referred to her clinician for confirmatory testing. We will not do hCG tests at the baseline visit, since many women will still have positive levels from pregnancy. If a woman is determined to be pregnant during the study year they will be censored at that timepoint. We do not anticipate any harm to participation even if a woman were to become pregnant during the study. 4) Waist Circumference: Per NHANES methodology.^[[46]](#endnote-46)^ 5) Blood pressure: Determined twice, five minutes apart in the seated position after 15 minutes of rest. Values will be averaged. 6) Biomarkers: HbA1c, hsCRP, adiponectin and fasting glucose, insulin, and lipids. 7) Potential mediators: Diet will be assessed by 2005 Block FFQ, administered online during the study visit. Physical activity will be assessed using an adapted Pregnancy Physical Activity Questionnaire (PPAQ).^[[47]](#endnote-47)^ Breastfeeding intensity and frequency will be assessed through a short questionnaire. 8) Potential moderators: Postpartum depression (PPD) will be assessed using the Edinburgh Postnatal Depression Scale (EPDS).^[[48]](#endnote-48)^ Women found to have PPD (defined as an EPDS score ≥12) will be assessed by a study clinician and offered a referral to services. They will be allowed to continue in the study. Any woman screening in for self-harm or harm to others will be immediately referred for mental health evaluation. We will assess appetite and sleep using real-time visual analog scales in the app. 9) Satisfaction: Likert scale for satisfaction and willingness to recommend to a friend.

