| **Table 3: Measurements**  **Variable** | **Day 1, 2, or 3 pp** | **Visit 1**  **(6 wks pp)** | **Visit 2**  **(6 months pp)** | **Visit 3**  **(12 months pp)** |
| --- | --- | --- | --- | --- |
| Demographics Questionnaire (Based on Behavioral Risk Surveillance System (BRFSS) |  | X |  |  |
| Height |  | X |  |  |
| Medical History Update |  | X | X | X |
| Urine hcg* |  |  | X | X |
| **Clinical Outcomes** | | | | |
| Weight |  | X | X | X |
| Waist circumference |  | X | X | X |
| Heart Rate |  | X | X | X |
| Blood Pressure |  | X | X | X |
| Fasting lipid profile |  | X | X | X |
| HbA1c |  | X | X | X |
| TSH |  | X | X | X |
| OGTT (only for GDM women) |  | X |  |  |
| Fasting glucose |  | X | X | X |
| Fasting insulin |  | X | X | X |
| Adiponectin |  | X | X | X |
| hsCRP |  | X | X | X |
| **Behavioral Outcomes** | | | | |
| Adapted Pregnancy Physical Activity Questionnaire (PPAQ) |  | X | X | X |
| 2005 Block FFQ |  | X | X | X |
| Breastfeeding Questionnaire |  | X | X | X |
| **Mediating Variables** | | | | |
| Social Support for Eating |  | X | X | X |
| Social Support for Exercise |  | X | X | X |
| Self Efficacy Survey for Diet and Exercise Behaviors |  | X | X | X |
| Readiness to Change Questionnaire |  | X | X | X |
| Perceived Stress Scale |  | X | X | X |
| Edinburgh Postnatal Depression Scale (EPDS) |  | X | X | X |
| Sleep Questionnaire |  | X | X | X |
| Satisfaction |  | X | X | X |

*NOTE: Subjects will not take a urine hcg test at 6 weeks because the hcg would be expected to be elevated from pregnancy and would not be able to identify a new pregnancy. All subjects will take a pregnancy test at every subsequent study visit. In addition, if subject reports new amenorrhea, the subject will be asked to come in for a pregnancy test. If results indicate exclusionary condition such as pregnancy, subject will be removed from study and referred for appropriate clinical follow-up care. These subjects will be excluded as they would affect study data and because these conditions may require different care. If a subject is diagnosed with diabetes at any visit, we will ask their permission to continue to follow them. Permission will be requested to obtain medical records for the pregnancy to look at recurrence of pregnancy complications in both groups.

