**Statistical Analysis**: The analysis for the primary outcomes will be intent-to-treat, using longitudinal mixed methods to account for loss to follow-up and censored participants. Due to the longitudinal nature of this study, we will assess the change in weight from the 6-week study visit to weight at 6 and 12 months by a mixed model analysis with an exchangeable correlation structure and adjustment for weight gain during pregnancy, and breastfeeding (a mediating effect). Within this model, we can further assess differences in weight between various time points by contrasts. We will also compare the delta weight prepregnancy to 6 and 12 months postpartum in the intervention group to the control group using a multivariate regression model, adjusting for age and race. Secondary clinical outcomes will be compared between groups by a generalized linear mixed model analysis, similar to the primary outcome analysis. When necessary, adjustment for multiple comparisons will be made. We will assess reach, effectiveness, and adoption per the RE-AIM model to prepare for a pragmatic trial (Table 2). We will use content-based analysis on focus group data to assess perceived barriers and facilitators to success of the intervention.

**Anticipated results**: Primary outcome: We expect that women who participate in the *Fit After Baby* program will demonstrate increased weight loss in the postpartum year vs. the Text4Baby control group. Secondary outcomes**:** We expect an improvement in cardiometabolic risk factors among women randomized to the Fit After Baby program. We anticipate that increased engagement and satisfaction will be associated with increased weight loss. We expect that decreased caloric intake relative to expenditure and increased physical activity will help to mediate weight loss. We anticipate that postpartum depression may interfere with weight loss as it will decrease engagement with the program, and appetite and sleep may also moderate weight loss.

| **Table 2: Relevant RE-AIM Outcomes** | **Measures/Data Source** | |
| --- | --- | --- |
| **REACH** | | |
| 1) Proportion of approached women agreeing to participate  2) Proportion of recruited women initiating program | | 1) Recruitment data  2) App usage data |
| **EFFECTIVENESS** | | |

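### The mixed model for weight change from the 6-week visit adjusts for breastfeeding, which the protocol itself calls a mediator, without limiting the adjustment to the pre-randomisation value

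*Protocol*

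**What the plan says.** The Statistical Analysis paragraph opens with "The analysis for the primary outcomes will be intent-to-treat, using longitudinal mixed methods to account for loss to follow-up and censored participants". It then describes a mixed model for change in weight from the 6-week visit to 6 and 12 months, with "adjustment for weight gain during pregnancy, and breastfeeding (a mediating effect" as the covariates. No version of this model without breastfeeding is described.

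Under Measures, item 7 begins "7) Potential mediators: Diet will be assessed by 2005 Block FFQ, administered online during the study visit" and goes on to say "Breastfeeding intensity and frequency will be assessed through a short questionnaire". Breastfeeding is thus called a mediator in two places. In Table 3 the row "Breastfeeding Questionnaire" is marked at Visits 1, 2 and 3.

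Section 5.6 fixes the time of assignment: "During the first study visit, all enrolled subjects will be randomized using previously described permuted block scheme to either control or intervention arm".

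Under Study Outcomes, "The primary outcomes are change in weight from baseline to 6 months and to 1 year postpartum (exit study visit", together with change from self-reported pre-pregnancy weight to one year. The pre-pregnancy comparison has its own regression, adjusted for age and race only. Secondary clinical outcomes are to be analysed with a model described as similar to the primary one.

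The power statement concerns a 4.2 kg difference in 12-month weight change and controls for baseline weight only.

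**The concern.** A mediator lies on the path from assignment to outcome. If the model conditions on it, the arm coefficient loses whatever part of the programme's effect runs through it. What remains is a partial effect, whereas the trial's hypothesis is about the result of being assigned to one programme or the other.

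There is a second route to distortion. If assignment changes breastfeeding, and breastfeeding shares unmeasured causes with weight (for example health, return to work or motivation), then women with the same breastfeeding level in the two arms differ in those causes. Randomisation no longer protects the comparison, and the resulting bias can go in either direction.

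Two practical consequences follow. The two primary comparisons use the same 12-month weights but may target different effects, so a disagreement between them could come from the outcome definition or from the covariate. The same adjustment may also be carried into the secondary models. The pilot is meant to supply preliminary data for a larger trial, so the meaning of its effect estimate matters.

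**Working it through.** **1. Timing.** Randomisation takes place at Visit 1 (section 5.6). Breastfeeding is recorded at Visits 1, 2 and 3 (Table 3). Two of the three measurements are therefore post-randomisation. Gestational weight gain, the other covariate, is fixed before randomisation and raises no difficulty.

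**2. Which value enters the model.** The text does not say. A value fixed before assignment cannot mediate the effect of assignment, so the label in the analysis paragraph fits only the Visit 2 and 3 values. If Visit 1 was meant, the label is wrong and the sentence still needs correcting.

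**3. The plan's own power figure.** Inputs from the power paragraph: 54 and 27 women, difference 4.2 kg, SD 5.7 kg. Alpha is not stated there; 0.05 two-sided is assumed.

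- Standard error = 5.7 × √(1/54 + 1/27) = 5.7 × 0.2357 = 1.34 kg.
- Standardised difference = 4.2 / 1.34 = 3.13.
- Power = 87.8% by the normal approximation and 87.0% by the exact noncentral t with 79 degrees of freedom.

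The stated figure of at least 87% reproduces. One-sided testing would give about 93%, so two-sided 0.05 is the implied level. The figure belongs to a comparison that controls for baseline weight and nothing measured later.

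**4. What conditioning on a mediator could do.** The documents give neither the effect of assignment on breastfeeding nor that of breastfeeding on weight. Everything in this step is assumption.

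If a share m of a 4.2 kg effect passes through breastfeeding, the adjusted model targets 4.2 × (1 − m). With SD held at 5.7 kg (exact t):

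| Assumed share | Effect targeted | Power |
|---|---|---|
| 0% | 4.20 kg | 87.0% |
| 10% | 3.78 kg | 79.4% |
| 20% | 3.36 kg | 69.5% |
| 30% | 2.94 kg | 58.0% |

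Alternatively, shift = (arm difference in breastfeeding) × (weight difference per unit of breastfeeding). Treating breastfeeding as yes or no, and assuming an arm difference of 10 to 30 percentage points and a weight difference of 1 to 4 kg:

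- Low end: 0.10 × 1 = 0.1 kg, which is 2% of 4.2 kg.
- High end: 0.30 × 4 = 1.2 kg, which is 29% of 4.2 kg.

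The whole of this range lies below one standard error of the planned comparison (1.34 kg).

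**5. Collider bias, also assumed.** Let assignment raise breastfeeding by 0.3 SD and let breastfeeding have no effect on weight. Let an unmeasured factor correlate 0.5 with breastfeeding and add 2 kg to weight per SD. With a true effect of −4.2 kg, the adjusted coefficient is −4.2 − (2 × 0.5 × 0.3) = −4.5 kg. A large simulation gave −4.52 kg. Here adjustment exaggerates the effect, whereas in step 4 it shrinks it.

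**6. When nothing happens.** If assignment does not affect breastfeeding, there is no indirect effect to remove and arm stays independent of the unmeasured causes given breastfeeding. Both distortions are then nil. That single condition is enough; the absence of shared causes is not needed as well.

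**The case against.** The best defence is that the mediator label is weak evidence of a real causal path. The protocol uses such labels loosely: the depression scale is a potential moderator under Measures but a mediating variable in Table 3, and Table 3 lists breastfeeding among behavioural outcomes. The anticipated-results text names energy balance and physical activity as the mediators of weight loss, not breastfeeding. None of the twelve weekly programme themes names breastfeeding. The control arm receives baby-care texts, so even the direction of any arm difference is unknown. Perhaps only the Visit 1 value was intended, and choosing the time point could be left to a statistical analysis plan.

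Much of this stands. It means that a distortion is possible but not shown. It does not rescue the sentence, because the protocol names the covariate for a primary model, calls it a mediator and sets no limit on which value is used. That is a choice made, not a detail left open.

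A reader might go further and infer three things that the documents do not support:

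- **That intent-to-treat is breached.** The paragraph states "The analysis for the primary outcomes will be intent-to-treat", and analysis by assigned arm is compatible with a poor covariate. What changes is the meaning of the coefficient.
- **That the trial is powered for one quantity and analyses another.** The 4.2 kg is reported only as observed in an earlier trial. Whether that figure was itself adjusted for breastfeeding cannot be checked here.
- **That the trial has no primary estimate of the total effect.** The comparison of change from pre-pregnancy weight does not condition on breastfeeding.

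**Conclusion.** The point holds for the mixed model of weight change from the 6-week visit, and for secondary models if they copy its covariates. Followed as most naturally read, the plan conditions the arm effect on a variable that it places on the causal path. If assignment affects breastfeeding, the coefficient is not the total effect of assignment and may also carry collider bias.

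Neither size nor sign can be derived from the documents. The shifts of 0.1 to 1.2 kg, and the power of 79% to 58% for mediated shares of 10% to 30%, rest wholly on assumed inputs and only show what such a shift would look like. The conclusion assumes that on-study breastfeeding enters the model, which the label suggests but the text does not state.

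The pre-pregnancy comparison, the adjustment for gestational weight gain and the sample-size arithmetic are sound on this point. In a pilot, this is a worthwhile and easy correction to what one primary estimate means; it is not grounds for calling the trial's results invalid.

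**What to change.** Revise the sentence that specifies the primary mixed model so that post-baseline breastfeeding is removed. Adjust only for pre-randomisation values: 6-week weight, gestational weight gain and, if wanted, breastfeeding at Visit 1, recorded before assignment is made known. Drop the mediator wording from that sentence.

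State that the same rule applies to the secondary outcome models described as similar. Place breastfeeding at 6 and 12 months in a separate exploratory mediation analysis, with its assumption of no unmeasured common causes stated.

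The cost is a sentence or two in the Statistical Analysis paragraph. No new data, visits or participants are needed. The 87% power statement can stand, since it already refers to a comparison controlling for baseline weight only.

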Recruitment targets and power calculation: We plan to recruit at least 7 participants per month, with a goal of consenting 140 subjects to account for recruitment yield of 50-70%. After 2 years we should have data from 81 participants at one year postpartum. With 54 subjects in the intervention group and 27 subjects in the control group, a 2-sample t-test controlling for baseline weight will have at least 87% power to detect a 4.2 kg difference between groups in 12 month weight change (the 4.2 kg difference with a pooled standard deviation of 5.7 kg was observed in the Balance after Baby RCT). This is adequate power for a pilot study designed to establish the foundation for a subsequent larger pragmatic trial of the *Fit After Baby* program.

+Structured interviews

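### Postpartum weight retention, a primary outcome, is given a separate age-and-race regression instead of the longitudinal mixed model promised for the primary outcomes, and the 6-week weight is left out

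*Protocol*

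**What the plan says.** The Study Outcomes paragraph (section 5.6) lists as primary the weight change from baseline to 6 months and to 1 year, and also "change in weight from self-reported pre-pregnancy weight to one year postpartum".

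The Statistical Analysis paragraph opens with a rule for all of these: "The analysis for the primary outcomes will be intent-to-treat, using longitudinal mixed methods to account for loss to follow-up and censored participants". It then treats them differently:

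- Change from the 6-week visit gets a mixed model with exchangeable correlation, adjusted for gestational weight gain and breastfeeding.
- For retention it says "We will also compare the delta weight prepregnancy to 6 and 12 months postpartum" between the arms, "using a multivariate regression model, adjusting for age and race".

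No other covariate is listed for the retention regression, and nothing is said about how it treats missing or censored weights.

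Three other statements bear on this. On timing, "During the first study visit, all enrolled subjects will be randomized", and Table 3 schedules a weight at that visit. On new pregnancies, the Measures paragraph says "If a woman is determined to be pregnant during the study year they will be censored at that timepoint". The power paragraph is built on 12-month data: "With 54 subjects in the intervention group and 27 subjects in the control group".

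**The concern.** Two separate matters arise in one sentence of the plan.

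**Model type.** One primary outcome is covered by a general promise of mixed methods and by a specific instruction to use a regression. The promise is justified by loss to follow-up and censoring, and these affect retention exactly as they affect change from baseline. A woman seen at 6 months and then lost or pregnant has a usable 6-month weight. A mixed model takes it in; an ordinary regression on the 12-month change has no response for her. The two primary results could then rest on different women and different covariates, and could differ for that reason alone.

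**Covariates.** Retention at 12 months is retention at the baseline visit plus the change after it. The first part is settled before randomisation, so treatment cannot alter it. Visit 1 may fall anywhere from 4 to 16 weeks postpartum (section 5.5), which can add to its spread. With the 6-week weight left out, that spread stays in the error term of the arm comparison, and a chance difference between 54 and 27 women is not corrected.

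**Working it through.** **1. The protocol's own figure.** Inputs from the power paragraph: 54 and 27 women, difference 4.2 kg, SD 5.7 kg. Alpha is not stated there; two-sided 0.05 is assumed.

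- Standard error = 5.7 × sqrt(1/54 + 1/27) = 5.7 × 0.2357 = 1.344 kg.
- Noncentrality = 4.2 / 1.344 = 3.126.
- Noncentral t with 79 df gives 87.0%; the normal approximation gives 87.8%.

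The stated value of at least 87% reproduces. It is the power of an unadjusted t-test at SD 5.7 kg, and it concerns 12-month weight change. The protocol gives no SD, effect or power for retention.

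**2. Decomposing the retention outcome.** Write P for pre-pregnancy weight, B for the 6-week weight and Y for the 12-month weight. Then Y − P = (B − P) + (Y − B). Let s be the SD of B − P, take 5.7 kg as the SD of Y − B, and let r be their correlation. Both s and r are assumptions, since neither is in the protocol.

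- SD without the 6-week weight = sqrt(s² + 5.7² + 2 × r × s × 5.7).
- Residual SD after adjusting for 6-week retention = 5.7 × sqrt(1 − r²).

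Example with s = 6 and r = 0: sqrt(36 + 32.49) = 8.28 kg; standard error 8.28 × 0.2357 = 1.95 kg; noncentrality 2.15; power 57%.

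**3. Results for 4.2 kg with 54 and 27 women (SD in kg, power).**

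| Assumed s | r = 0 | r = -0.3 | r = -0.5 |
|---|---|---|---|
| 3 kg, unadjusted | 6.44, 78% | 5.59, 88% | 4.94, 95% |
| 4 kg, unadjusted | 6.96, 71% | 5.90, 85% | 5.07, 93% |
| 6 kg, unadjusted | 8.28, 57% | 6.93, 72% | 5.86, 85% |
| 8 kg, unadjusted | 9.82, 43% | 8.31, 56% | 7.13, 69% |
| Any s, adjusted | 5.70, 87% | 5.44, 90% | 4.94, 95% |

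Adjusted power is never below unadjusted power in these scenarios. The degrees of freedom used up by the covariates do not change the rounded values. The table counts the same 81 women in both analyses, so any gain from using 6-month weights of women without a 12-month weight is not in it.

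**4. Size of a chance imbalance.** The standard error of the arm difference in B − P is s × 0.2357: 0.7 kg at s = 3 and 1.9 kg at s = 8, beside a target difference of 4.2 kg.

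**5. One effect on two scales.** Suppose Y − B is regressed on arm, B and P. Adding B − P to the response gives Y − P. Since B − P is a linear combination of covariates already in the model, only the coefficients of B and P change; the arm coefficient and its standard error do not. With both weights as covariates, the 12-month arm difference is therefore the same number from either origin.

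**The case against.** The strongest reply is that only the model name is inconsistent and the rest is preference. Four parts of it deserve an answer.

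- *A reader might infer that women without the visit are dropped.* The protocol states no complete-case rule. It describes one multivariate regression for both time points, which could mean a joint model, and missing-data detail may sit in an analysis plan that is not shown. This stands: exclusion is what an ordinary regression on the 12-month change would do, not something the protocol says. What remains is that the protocol names a different method from the one it promised, and states no mechanism by which that method meets the promise.
- *A reader might infer a breach of intent-to-treat.* A regression that compares women by randomised arm is not one, and leaving out a baseline covariate has no bearing on it. The conflict is only with the mixed-method, loss-to-follow-up part of the sentence.
- *Omitting the 6-week weight is not an error.* It causes no bias under randomisation, and chance imbalance is already reflected in the standard error. The power paragraph's reference to baseline weight concerns 12-month weight change, and the mixed model does not list the 6-week weight as a covariate either. All true; the point is precision only.
- *The remedy merges two outcomes that the hypothesis keeps apart.* It does make one 12-month test of them. But the two differ only by a quantity fixed before randomisation, so treatment has one effect to show, and retention by arm can still be reported.

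**Conclusion.** The inconsistency is in the text and does not depend on any calculation: one primary outcome has two analysis methods, and the specific one comes with no stated way to account for loss or censoring. It is worth correcting in the protocol, since an analysis plan would otherwise have to depart from one of the two statements.

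The covariate point concerns efficiency. Its size is uncertain because it depends on an assumed 6-week retention SD (3 to 8 kg), an assumed correlation with later change, an SD of 5.7 kg for later change and a 4.2 kg effect borrowed from the 12-month weight-change calculation. Across that range, unadjusted against adjusted power is 78% to 43% against 87% at correlation 0, 88% to 56% against 90% at -0.3, and 95% to 69% against 95% at -0.5. A reader might take the low figures as the trial's actual power for retention; the protocol does not supply what is needed to say so, and the loss may be close to nil. Adjustment did not lower power in any scenario.

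**What to change.** In the Statistical Analysis paragraph, replace the separate regression for retention. Analyse 6- and 12-month weight in the same longitudinal mixed model as change from baseline, with 6-week weight and self-reported pre-pregnancy weight as covariates; age and race may stay. Report adjusted mean retention by arm at both times. State that, with both weights and otherwise the same covariates on each scale, the 12-month arm difference is identical from either origin, so it is one test reported on two scales.

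If the separate regression is kept, the least that is needed is a statement of how it treats missing and censored weights, together with the 6-week weight as a covariate.

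The cost is wording. The 6-week weight is in Table 3 and pre-pregnancy weight is collected by self-report, so no new measurement, visit or participant is needed. The one matter to accept openly is that the two 12-month comparisons no longer count as separate tests.
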